## Abstract

This protocol aims to profile the pharmacokinetics of metformin and *Andrographis paniculata* (AP) and continue with untargeted pharmacometabolomics analysis on pre-dose and post-dose samples to characterise the metabolomics profiling associated with the human metabolic pathways. This is a single-centre, open-labelled, three periods, crossover, randomised-controlled, single-dose oral administration pharmacokinetics and metabolomics trial of metformin 1000 mg (*n* = 18), AP 1000 mg (*n* = 18), or AP 2000 mg (*n* = 18) in healthy volunteers under the fasting condition. Subjects will be screened according to a list of inclusion and exclusion criteria. Investigational products will be administered according to the scheduled timeline. Vital signs and adverse events will be monitor periodically, and standardized meals will be provided to the subjects. Fifteen blood samples will be collected over 24 h, and four urine samples will be collected within a 12 h period. Onsite safety monitoring throughout the study and seven-day phone call safety follow-up will be compiled after the last dose of administration. The plasma samples will be analysed for the pharmacokinetics parameters to estimate the drug maximum plasma concentration. Untargeted metabolomic analysis between pre-dose and maximum plasma concentration (Cmax) samples will be performed for metabolomic profiling to identify the dysregulation of human metabolic pathways that link to the pharmacodynamics effects. The metformin arm will focus on the individualised Cmax plasma concentration for metabolomics study and used as a model drug. After this, an investigation of the dose-dependent effects will be performed between pre-dose samples and median Cmax concentration samples in the AP 1000 mg and AP 2000 mg arms for metabolomics study. The study protocol utilises a crossover study design to incorporate a metabolomics-based study into pharmacokinetics trial in the drug development program. The combination analyses will complement the interpretation of pharmacological effects according to the bioavailability of the drug.

## 1. Introduction

Phase one trials aim to estimate the pharmacokinetics and pharmacodynamics of the investigational products, measure drug activity, and estimate the initial safety and tolerability [1]. According to the clinicaltrials.gov database, it was found that 1.5% of early-phase clinical trials applied metabolomics investigation in the studies from 2004 to 2015 [2]. The application of metabolomics in drug discoveries includes the investigation of a drug’s mechanism of action, identify the drug targets and monitor efficacy outcomes [3]. Pharmacometabolomics could be used to identify relevant biomarkers and validate the complex methodology in the early drug development process. Metabolomics analyses the end-products of the cellular reactions, closely related to the phenotype [4]. In the discovery and development of drugs, the metabolomics approach enables diagnostic biomarker identification, drug target screening in absorption, disposition, metabolism, elimination and toxicity, and applications in clinical trials to monitor pharmacological as well as adverse effects [5].

Herbal medicine is a multi-components therapeutic that combines various compounds interacting with multiple targets to produce the optimum pharmacological effects [6]. Single biomarker monitoring is no longer sufficient to evaluate the therapeutic effects of high-dimensional treatment methods from herbal medicine. Integrating metabolomics and pharmacokinetics to study multi-component drugs has expanded the application of metabolomics in both drugs and herbal medicine [7]. Various studies have included metabolomics-based research in the pharmacokinetic studies of single chemicals and multi-components drugs [8]. The incorporation of metabolomics study into an early-phase pharmacokinetic study could simultaneously quantitate the rate and extent of drug absorption into the human blood circulation and explore the metabolic pathway involved in the early-phase clinical trial.

Metformin is a well-known first line antidiabetic therapeutic agent that have established safety profiles, the mechanism of action is inconclusive. The common side effects are generally related to gastrointestinal and the effects are reversible [9]. The pharmacokinetic parameters for metformin 1000 mg includes the maximum plasma concentration (Cmax) of 1560 ng/mL, the area under the plasma drug concentration time curve (AUC_0-infinity_) of 9360 ng*h/mL, and time to reach Cmax (Tmax) of 2.5 h [10]. AP is a herbal medicine from the Acanthaceae family found in Southern and Southeast Asia [11] with several pharmacological activities including antidiabetic, anti-inflammatory, antibacterial, antiviral, and others [12]. There are several A. paniculata products registered with the Ministry of Health Malaysia as traditional medicines without therapeutic claims. The major bioactive compounds for this multi-component medicinal plant includes andrographolide, deoxyandrographolide, neoandrographolide, 14-deoxy-11,12-didehydroandrographide, and isoandrographolide [13]. A meta-analysis of ten randomised controlled clinical trials demonstrated that AP is generally safe, and the common adverse events for AP are gastrointestinal disorder, skin, and subcutaneous disorder [14]. Several pharmacokinetic trials have been conducted using an AP of fixed combination for andrographolide [15,16,17]. One study investigated up to four major compounds for AP using multiple doses in healthy volunteers, the Cmax for andrographolide was 32.41 ng/mL, and the Cmax for 14-deoxy-11,12-didehydroandrographolide was 44.89 ng/mL [18]. A clinical trial conducted in Malaysia using AP capsules up to 1200 mg for 12 weeks significantly reduced HbA1c by 5.46% [19]. Due to insufficient clinical data associated with the pharmacokinetics of AP and its pharmacological effects, the registration of herbal medicine with therapeutic claims remains a challenge. The quality and consistency of major phytochemicals in herbal medicines affect the pharmacokinetic profiles. As a result, we performed a pharmacokinetics and metabolomics study in a similar group of healthy volunteers from the same batch of investigational products.

The phase one study aims to find an optimal dose through dose escalation in several cohorts [20]. This is a proof-of-concept study to explore the integration of the metabolomic study and the pharmacokinetic study in early-phase clinical trial. In the phase 1 trial, clinical monitoring, continuous laboratory parameters, and pharmacokinetics study are performed to determine dose-escalation. Metabolomic profiles obtained before, during, or after dosing provide insights about the drug mechanism of action and variation in the response to treatment [21]. The application of a metabolomic study in the early-phase clinical trial has the advantage of a small, short, and underpowered design, however, pharmacometabolomics can help reduce the variability of the study populations and act as a powerful surrogate of drug response in the identification of perturbed human metabolic pathways and explore provisional therapeutic or safety biomarkers [2].

In the bioanalytical analyses, metformin will be used as a model drug for individualised pharmacokinetic and metabolomic analyses to identify dysregulated human metabolic pathways. Then, AP arms will follow a similar analysis framework with an exploration of the additional dose-dependent effects. This study utilises a crossover design to reduce the intra-subject variability to compare the metabolomics of the metformin and AP formulations. Both medicines exhibit antidiabetic effects from the literature, so the human metabolic pathways related to antihyperglycemic effects using pharmacometabolomics will be explored.

### Objectives

The study aimed to determine the safety of metformin 1000 mg, AP capsules 1000 mg, and AP capsules 2000 mg in the clinical part.

In the pharmacokinetics and metabolomics analyses, metformin 1000 mg will be used as a model drug for the determination of the pharmacokinetic parameters including the Cmax, Tmax, half-life (T1/2), and AUC0-infinity. The individualised Cmax of metformin will be used for the metabolomics analyses to identify dysregulated human metabolic pathways that are associated with diabetic effects.

The AP 1000 mg and AP 2000 mg analyses will follow the pharmacokinetics and metabolomics framework from the metformin arm in the second analysis. The pharmacokinetics for AP 1000 mg and AP 2000 mg will be compared for the three bioactive compounds, andrographolide, neoandrographolide, and deoxyandrographolide. The dysregulated human metabolic pathways identified from the metabolomics analyses for two doses will be compared based on the dose-dependent effects. 

Finally, the dysregulated human metabolic pathways associated with the diabetic effects will be compared for all three intervention arms.

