#### 2.3.7. Screening and Data Collection

Subjects will be screened for the eligibility criteria according to the screening case report form after signing the informed consent form. The principal investigator will perform the physical examination, review the demographic data, electrocardiogram, vital signs, biochemistry, haematological, serological, urinalysis test, and perform the interview questionnaire to determine the subject’s eligibility. Eligible subjects will attend the dosing day at the trial site and will be asked to fast for at least ten hours to reduce the variability of drug absorption. Eligible subjects will then be asked to attend a method validation visit to collect additional blood and urine samples.

On the dosing day, the study coordinator will record the subject attendance list, subject enrolment list, subject identification list, and subject randomisation sheet. Subjects will be assigned to the randomisation group by the study coordinator. Pre-dose urine samples and plasma samples will be collected before dosing. After single-dose oral administration, fourteen blood samples will be collected at 0.5, 1, 1.5, 2, 2.5, 3, 3.5, 4, 5, 6, 8, 10, 12, and 24 h post-dose. The actual sampling time will refer to the subject plasma sampling schedule (Supplementary Figure S6) and subject urine sampling schedule. An indwelling intravenous cannula will be used to collect the pre-dose and up to 12 h post-dose blood sample by syringe. The blood samples will then transferred into a pre-labelled potassium ethylenediaminetetraacetic acid (KEDTA) tube. The heparin-lock technique will be performed to prevent clotting of the blood by injecting 1 mL of heparinised saline in the indwelling cannula. Ambulatory blood will be collected at 24 h post-dose. The blood samples will then be centrifuged at 35,000 rpm for 15 min at 20 °C, and the plasma separated into three aliquots in cryotubes and stored at −80 °C in a freezer. The post-dose urine samples will be collected at three periods: period U1 (0–4 h post-dose), U2 (4–8 h post-dose), and U3 (8–12 h post-dose. The urine samples will then be separated into three aliquots in cryotubes and stored at −80 °C in a freezer. The study activities will be recorded on the case report form.

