Food intake will be standardized throughout ward stay. Subjects will be provided with lunch at 12.20 pm, a tea break at 4.30 pm, and dinner at 7 pm. The calorie count for the main meal will be maintained at approximately 600 kcal and the tea break calories at around 350 kcal. Meal intake start time and end time will be recorded on the meal monitoring form.

The biological samples will be segregated according to the individual subjects for all of the sampling time points and processing batches after the study is completed. The details of the plasma segregation activities will follow the procedures according to the plasma and urine sample segregation forms.

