### 2.4. Safety Assessment

The principal investigator will stay on-site to monitor any adverse events during the ward stay. Vital signs will be monitored every two hours at 10 a.m., 12 p.m. and 2 p.m. Any complaint from the subjects will be directly recorded into the case report form for adverse event classification. An adverse event that occurs will be classified according to the clinical safety data management guidance [41].

Stopping rules and the continual reassessment method should be applied to phase one dose-escalation trials [42,43,44]. However, the stopping rules will not be implemented in this study for the following reasons: the investigated products are registered medicines, and the administered dose will be according to the regulatory approved dose. The study will involve antidiabetic drugs taken under the fasting condition, and lunch will be given four hours post-dose. Although metformin does not pose a hypoglycaemia risk, additional random plasma glucose monitoring will be performed every half an hour up to four hours to monitor the hypoglycaemia effect [45]. In the case a clinically significant hypoglycaemia event is determined by the investigator, 20 g of glucose water will be given to the subject at any point in time.

Physical examinations will be performed on all subjects before being discharged from the ward. At the end of the last dosing period, the biochemistry, haematology, and urinalysis will be performed to ensure the subjects’ safety before being discharged. A post-study phone call follow-up will be made seven days after the last dose of the last visit for adverse event monitoring.

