### 3.3. Untargeted Metabolomics and Multivariate Data Analysis

In the metformin analyses, pharmacometabolomics analysis will be performed to explore the human metabolic pathways between the pre-dose and peak plasma concentration. The samples will be analysed using Agilent LCMS-QTOF for an untargeted metabolomics approach following the literature method with some modification [47]. The samples will be analysed using a reverse phase column with a guard column in both the positive and negative modes. The instrument method setting will follow the METLIN analysis methods [48]. The pool quality control samples will be used to condition the column and visualisation checking for the batch analysis.

The untargeted metabolomics workflow is presented in Supplementary Figure S8. The chromatograms will be converted to the mzXML file using Global Natural Products Social (GNPS) package, University of California San Diego, California, United States [49]. MS spectral processing, normalisation, batch correction, multivariate analysis, and functional metabolic pathway analysis will be run on MetaboAnalyst web-based application (McGill University, Montreal, QC, Canada) to identify the human metabolic pathways [50]. In the multivariate analyses, principal component analysis (PCA) and partial least square discriminant analysis (PLSDA) will be used to inspect the region’s separation among the analysed time points. After this, a t-test will be used to identify the significantly differentiated compounds between the two-time point groups. The significant features will be processed in MS peaks to a pathway module to identify the dysregulated human metabolic pathways according to the Kyoto Encyclopaedia of Genes and Genomes (KEGG) database.

A similar analysis framework for metformin as described above will be repeated for AP 1000 mg and AP 2000 mg. There will be a head-to-head comparison of the pharmacokinetic profiles for both the AP arms. After this, the pharmacometabolomic identified dysregulated human metabolic pathways will be compared for the two doses in AP to investigate the dose-dependent effects. Finally, the dysregulated human metabolic pathways associated with the diabetic effects for the metformin, AP 1000 mg, and AP 2000 mg will be compared.

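### Metformin metabolomics: each subject's own Cmax sample has no pre-meal limit, so a peak at 5 h or later compares a fed sample with a fasted baseline and mainly costs power

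*Protocol article*

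**What the plan says.** All references are to the protocol article.

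- **Sample used, metformin.** Objectives: "The individualised Cmax of metformin will be used for the metabolomics analyses to identify dysregulated human metabolic pathways that are associated with diabetic effects". The Abstract, section 2.1 and the Discussion repeat the individual-peak rule. None of them sets a latest time or a feeding state.
- **Sample used, AP arms.** The Abstract gives a different rule, a comparison "between pre-dose samples and median Cmax concentration samples in the AP 1000 mg and AP 2000 mg arms".
- **Comparison and test.** Section 3.3 sets out to "explore the human metabolic pathways between the pre-dose and peak plasma concentration", and then "a t-test will be used to identify the significantly differentiated compounds between the two-time point groups".
- **Baseline state.** Section 2.3.7: subjects "will be asked to fast for at least ten hours to reduce the variability of drug absorption". The pre-dose sample is therefore fasted.
- **Meals.** Section 2.4: "The study will involve antidiabetic drugs taken under the fasting condition, and lunch will be given four hours post-dose". Section 2.3.7 puts lunch at 12.20 pm and adds "The calorie count for the main meal will be maintained at approximately 600 kcal".
- **Blood sampling.** Section 2.3.7 lists 14 post-dose samples: eight from 0.5 to 4 h, then 5, 6, 8, 10, 12 and 24 h.
- **Rescue glucose.** Section 2.4: if the investigator determines a clinically significant hypoglycaemia event, "20 g of glucose water will be given to the subject at any point in time". No consequence for the choice of metabolomics sample is stated.

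**The concern.** Followed literally, the metformin rule picks the post-dose sample by concentration alone. Most subjects should peak well before lunch and give a fasted sample. A late absorber gives a post-meal sample, and it enters the same t-test against a fasted baseline. Feeding state then differs between subjects within one comparison. That is not the same as prolonged fasting, which affects every subject in a similar way.

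A meal acts on glucose-related metabolism, which is where the trial looks for its diabetes-associated pathways. No untreated period exists from which a meal effect could be estimated and removed. At stake is the sensitivity of the metformin analysis, which serves as the model for the rest of the study.

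**Working it through.** The 18 subjects per formulation (section 2.3.6) come without alpha, power, effect size or SD, so there is no planned figure to reproduce. The check takes n = 18 as given.

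**Step 1. Feeding state by sampling time.** Lunch at 12.20 pm and 4 h post-dose implies dosing at about 8.20 am. The eight samples up to 4 h are fasted and the six from 5 h on are fed. The stated metformin Tmax is 2 h (section 2.1) or 2.5 h (Introduction), so a typical peak falls 1.5 to 2 h before lunch.

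**Step 2. How many late peaks.** Inputs: median Tmax m = 2 or 2.5 h, from the article. Assumptions: lognormal shape, CV 30% to 50%, and a peak recorded at 5 h when the true Tmax exceeds 4.5 h.

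- σ = √ln(1 + CV²)
- p = 1 − Φ(ln(4.5/m)/σ)
- expected number = 18p; P(at least one) = 1 − (1 − p)^18; P(at least 3) and P(at least 4) from the binomial (18, p)

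Example, m = 2.5 and CV 40%: σ = √ln 1.16 = 0.385; ln 1.8 = 0.588; 0.588/0.385 = 1.526; p = 0.0635; 18p = 1.14; 1 − 0.9365^18 = 0.69.

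| Median (h) | CV | p | Expected of 18 | P(≥1) | P(≥3) | P(≥4) |
|---|---|---|---|---|---|---|
| 2.0 | 30% | 0.003 | 0.05 | 5% | <0.1% | <0.1% |
| 2.0 | 40% | 0.018 | 0.32 | 27% | 0.4% | <0.1% |
| 2.0 | 50% | 0.043 | 0.77 | 55% | 4% | 0.6% |
| 2.5 | 30% | 0.023 | 0.41 | 34% | 0.7% | 0.06% |
| 2.5 | 40% | 0.064 | 1.14 | 69% | 10% | 2.4% |
| 2.5 | 50% | 0.107 | 1.92 | 87% | 30% | 11.8% |

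Counting every true peak after 4 h instead of 4.5 h raises the expected number to 0.16 to 2.88 over the same grid.

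**Step 3. Can fed samples create a false feature?** Take a paired t-test (the article does not state pairing) on a feature the drug does not change, with k of n differences carrying a common shift D. For large D the mean is kD/n and the SD is D√[k(n − k)/(n(n − 1))], so

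t → √[k(n − 1)/(n − k)] = √[17k/(18 − k)].

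This gives 1.00, 1.46, 1.84 and 2.20 for k = 1, 2, 3 and 4, against a two-sided 5% critical value of 2.11 (17 df). Simulated rejection of a null feature (100,000 runs, shifts of 1 to 10 SD):

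| Fed samples | Rejection at nominal 5% |
|---|---|
| 1 | 0.3% to 5.0% |
| 2 | 2% to 9% |
| 3 | 8% to 18% |
| 4 | 11% to 56% |

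One fed sample does not raise the false-positive rate. Clear inflation starts at three or four.

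**Step 4. Can a fed sample hide a true feature?** Same test, assumed true effect 0.8 SD, one fed sample with an assumed shift:

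| Shift of the one fed sample | Power |
|---|---|
| none | 89% |
| 3 SD against the effect | 55% |
| 5 SD against the effect | 18% |
| 10 SD against the effect | about 0% |
| 5 SD with the effect | 89% |
| 10 SD with the effect | 63% |

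The loss is large when the meal pushes against the drug effect. That is plausible for glucose-related features under an antihyperglycaemic drug.

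**The case against.** **Scope.** A reader might infer that the whole metabolomics endpoint is affected. The documents do not support that. The Abstract assigns median Cmax samples to both AP arms, and section 2.1 gives an AP Tmax of 1.63 to 2 h. A sample chosen that way falls before lunch and does not follow an individual late absorber. This objection stands.

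**False drug effects.** A reader might also infer that a fed sample will be reported as a drug effect. One subject moved by 10 SD does shift the mean change by 10/18 = 0.56 SD, but the same outlier inflates the SD, and t cannot pass about 1. The 69% and 87% in the table are chances of at least one fed sample, not of a false finding. Four or more have a chance of 0% to 12%. This objection also stands.

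**Rescue glucose.** Section 2.4 says metformin poses no hypoglycaemia risk, and the glucose would have to precede that subject's peak. For metformin this route should be rare. It merits a clause in the rule and no more.

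**Assumed spread.** The article gives no between-subject spread for Tmax, and the range of 5% to 87% is driven by the assumed CV. This is correct and limits how firmly the size can be stated.

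**Condensed article.** Section 2.2 cites a full protocol, version 4.0, which is not shown and might contain a limit. That is possible. But the article states its selection rule several times as the defining method, and that rule, read with the stated lunch and sampling times, lets fed and fasted samples mix. The point rests on what is printed.

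**Conclusion.** The point holds for the metformin comparison only. The stated rule admits a fed post-dose sample whenever a subject's highest concentration falls at 5 h or later. With an assumed lognormal Tmax (median 2 to 2.5 h, CV 30% to 50%), that is 0.05 to 1.9 of 18 subjects.

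The main harm is added variance and lost power on the features the trial targets. With one opposing fed sample, power falls from 89% to 55% (3 SD) or 18% (5 SD). These figures assume a paired test, a true effect of 0.8 SD and the stated shifts, none of which the article gives. A shift in the same direction as the drug effect costs nothing at 5 SD. Inflation of false features needs about three or four fed samples. Three or more have a 30% chance only in the most extreme case considered, and 10% or less in the others.

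The study is exploratory and the typical peak is fasted, so this is a modest, cheaply corrected weakness in the sample-selection rule.

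**What to change.** Add one sentence to the metabolomics analysis rule in section 3.3. The main metformin analysis uses only Cmax pairs whose post-dose sample was drawn before lunch (up to 4 h) and before any glucose was given. Keep every subject's pharmacokinetic data, and report the metabolomics result with and without the excluded pairs. For the AP arms, exclude only samples drawn after glucose.

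This changes the analysis set and leaves dosing, meals, sampling and rescue as they are. Section 2.3.7 already records meal start and end times, and section 3.1 records actual sampling times, so the rule needs no new data. The cost is the possible loss of one or two subjects from the main metformin metabolomics set.
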